#### Secondary outcome measures

Percentage of subjects with LSM by VCTE ≥ 8 kPa in the subgroup of patients with risk factors for chronic liver diseases at visit 1 and/or 2.Comparison of liver fibrosis diagnosis accuracy between VCTE and fibrosis scores (including NAFLD fibrosis score, FIB-4, Forns index and APRI score) in the general population and in the subgroup of patients with risk factors for chronic liver disease, at visit 1 and 2.Comparison of liver fibrosis diagnosis accuracy between VCTE, fibrosis scores and liver biopsy in the general population and in the subgroup of patients with risk factors for chronic liver diseases, in patients with a liver biopsy available at visit 2.Percentage of subjects with controlled attenuation parameter (CAP) ≥ 250 dB/m, either with M or XL probe, in the general population and in the subgroup of patients with risk factors for chronic liver diseases at visit 1 and/or 2.Comparison of liver steatosis diagnosis accuracy between CAP and steatosis scores (including fatty liver index (FLI), hepatic steatosis index (HSI), lipid accumulation product (LAP), index of NASH (ION) and NAFLD-liver fat score (NAFLD-LFS)) in the general population and in the subgroup of patients with risk factors for chronic liver diseases at visit 1 and 2.Comparison of liver steatosis diagnosis accuracy between CAP, steatosis scores (including FLI, HSI, LAP, ION and NAFLD-LFS) and liver biopsy in the general population and in the subgroup of patients with risk factors for chronic liver diseases, in patients with liver biopsy available at visit 2.Comparison of liver steatosis diagnosis accuracy between CAP and abdominal ultrasound in the general population and in the subgroup of patients with risk factors for chronic liver diseases, in patients with abdominal ultrasound available at visit 2.Comparison of values obtained with M and XL probes in the assessment of LSM and CAP using VCTE at visit 2.Cost-effectiveness and budgetary impact of a liver fibrosis screening program for liver fibrosis detection in the general population and in the subpopulation with risk factors for chronic liver diseases. Direct and indirect cost savings of early detection of liver fibrosis in subjects with risk factors for chronic liver diseases.Percentage of measurement failure during VCTE examination at visit 1 and 2.Percentage of patients with procedure-related adverse events (adverse events related to VCTE and/or liver biopsy) and serious adverse events during the duration of the study.Detection of common genetic variants, single nucleotide polymorphisms (SNPs), in patients with and without significant hepatic fibrosis or chronic liver diseases, including genome-wide association studies (GWAS) and whole-genome sequencing (WGS) in blood samples.Incidence of cirrhosis, liver cancer, and liver-related death and all-cause of mortality in patients with significant fibrosis and/or severe steatosis after 5 and 10 years from the first evaluation.Incidence of cardiovascular events in patients with significant fibrosis and/or severe steatosis after 5 and 10 years from the first evaluation.

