### Study design

This study is a single group screening study. It has been registered retrospectively on Clinicaltrials.gov (NCT03789825) the 14^th^ of November 2018. First patient included was in May 2018.

The present population-based study will include 30,000 subjects in eight European countries (Fig. 1). Eligible participants will be invited to attend at their primary care centre or at a research facility where a nurse will perform visit 1. This visit will include a detailed interview, physical examination, questionnaires related to alcohol consumption, quality of life and health status assessment, venipuncture for liver biochemical tests assessment and biobanking, and VCTE to assess LSM and controlled attenuation parameter (CAP). If participants show a LSM ≥ 8 kPa, unreliable or failed VCTE measurement [16] and/or increased ALT levels (ALT ≥ 1.5 x upper limit of normal value), they will be referred to second visit in a Liver Unit at the academic center for further evaluation (visit 2). Otherwise, the study finishes after completion of visit 1 (Fig. 2). Visit 2 will be completed by hepatologists within the 3 months following visit 1, according to a standardized work-up for liver disease diagnosis and evaluation. Visit 2 will include evaluation of the participant’s medical history, physical examination with complete liver tests, FibroScan examination and abdominal ultrasound. The FibroScan examination at visit 2 will be performed with both probes (M and XL). Afterwards, a liver biopsy will be offered to the patient for diagnosis and staging of liver disease when LSM is above 8 kPa or if chronic liver disease is suspected, as per standard of care.

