#### Sample size calculation

The sample size for the LiverScreen project has been computed to answer the questions of 1/ the usefulness of TE as a screening method to detect significant liver fibrosis among the European general population ≥ 40 years, and 2/ the differences (if any) in the 5-year incidence of liver clinical outcomes (or cardiovascular events or mortality) between those with and without significant liver fibrosis (LSM ≥ 8 kPa). Because the gold standard for the staging of liver fibrosis remains liver biopsy, the sample size calculation of the study considers the final number of liver biopsies needed to evaluate the concordance between liver biopsy and VCTE. For an estimated prevalence of LSM ≥ 8 kPa of around 3%, assuming a 5% of bilateral alpha error and a statistical power of 95%, a sample size of 28,887 subjects would be required. If 3% of the study population have altered VCTE and only 50% of them agree to have a liver biopsy performed, we will have around 450-500 available liver biopsies. Considering all these factors, the sample size of the study will be of 30,000 subjects.

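### Biopsy is reachable only through referral, so sensitivity, specificity, NPV and agreement of LSM with biopsy in the general population are not identified; the design supports PPV and confirmed yield

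*Protocol article*

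**What the plan says.** Under Secondary outcome measures, the protocol article lists "Comparison of liver fibrosis diagnosis accuracy between VCTE, fibrosis scores and liver biopsy in the general population" and in the risk-factor subgroup, then confines it to participants who have a visit-2 biopsy. A parallel outcome reads "Comparison of liver steatosis diagnosis accuracy between CAP and abdominal ultrasound in the general population", confined in the same way to those with a visit-2 ultrasound.

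Under Study design, visit 2 is for participants with LSM ≥ 8 kPa, a failed or unreliable VCTE, or ALT ≥ 1.5 x ULN. Everyone else finishes at visit 1. At visit 2, "a liver biopsy will be offered to the patient for diagnosis and staging of liver disease when LSM is above 8 kPa" or when chronic liver disease is suspected.

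Under Sample size calculation, the plan says that it takes into account "the final number of liver biopsies needed to evaluate the concordance between liver biopsy and VCTE". It derives that number as follows: "If 3% of the study population have altered VCTE and only 50% of them agree to have a liver biopsy performed", about 450 to 500 biopsies result.

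Under Statistical analyses, concordance with biopsy is planned without a named statistic. Sensitivity, specificity and predictive values are named for the fibrosis scores, with LSM ≥ 8 kPa as the reference.

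**The concern.** Whether a participant receives the reference standard depends on the index test. The table of LSM against biopsy has a well-filled positive row. Its negative row is empty or holds only people sent on for raised ALT or suspected disease. This is partial verification, and part of the LSM-negative group has no chance at all of being verified.

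The rationale section faults earlier studies for not confirming the diagnosis systematically by biopsy, and the Discussion promises answers on diagnostic accuracy in a low-prevalence setting. Because LSM itself is the reference for the fibrosis scores, biopsy is the only independent histological check on LSM. A sensitivity or agreement figure taken from the biopsied set and labelled as general-population accuracy would largely reflect who was biopsied.

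**Working it through.** **Inputs from the protocol article (Sample size calculation).** N: "the sample size of the study will be of 30,000 subjects". LSM ≥ 8 kPa: 3%. Biopsy acceptance among positives: 50%.

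**Assumptions (not in the documents).** PPV of LSM ≥ 8 kPa against biopsy: 30% to 70%, with 50% for illustration. Number k of LSM-negatives biopsied: 0 to 291. Share q of those with fibrosis: 10% to 30%. Fibrosis rate r among all LSM-negatives: 0% to 3%.

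**1. The plan's own figure.** 30,000 x 0.03 = 900 positives; 900 x 0.50 = 450 biopsies. This matches the lower end of the stated range, and all of them come from positives. LSM-negatives: 30,000 − 900 = 29,100.

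**2. Biopsies from positives only.** Let TP, FP, FN and TN be the true population counts.
- Naive sensitivity = 0.5TP / (0.5TP + 0) = 100%.
- Naive specificity = 0 / (0.5FP + 0) = 0%.
- Raw agreement = 0.5TP / 450, which is simply the PPV.

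The first two hold whatever the true accuracy.

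**3. Some LSM-negatives biopsied.** At PPV 50%, the 450 biopsied positives split 225/225. Naive sensitivity = 225 / (225 + kq). Naive specificity = k(1 − q) / (225 + k(1 − q)).

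| k | q | Naive sensitivity | Naive specificity |
|---|---|---|---|
| 50 | 10% | 225/230 = 97.8% | 45/270 = 16.7% |
| 50 | 30% | 225/240 = 93.8% | 35/260 = 13.5% |
| 150 | 10% | 225/240 = 93.8% | 135/360 = 37.5% |
| 150 | 30% | 225/270 = 83.3% | 105/330 = 31.8% |

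A second example fixes the truth at TP 360, FP 540, FN 240, TN 28,860: sensitivity 60%, specificity 98.2%. Half of the positives (180 and 270) and 291 negatives are biopsied.
- Negatives taken at random (2.4 with fibrosis): 180/182.4 = 98.7% and 288.6/558.6 = 51.7%.
- 20% of them with fibrosis: 180/238.2 = 75.6% and 232.8/502.8 = 46.3%.
- 30% of them with fibrosis: 180/267.3 = 67.3% and 203.7/473.7 = 43.0%.

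In general, naive specificity is too low whenever true negatives are biopsied at a lower rate than the 50% of positives, which is certain here. Naive sensitivity is too high only if missed cases are also biopsied at a rate below 50%.

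**4. What the unverified group leaves open.** At PPV 50% there are 450 true positives among the 900. Sensitivity = 450 / (450 + 29,100r).

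| r | Missed cases | Sensitivity |
|---|---|---|
| 0% | 0 | 100% |
| 0.1% | 29 | 94% |
| 0.5% | 146 | 76% |
| 1% | 291 | 61% |
| 2% | 582 | 44% |
| 3% | 873 | 34% |

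Over the same range, specificity = 29,100(1 − r) / (29,100(1 − r) + 450) moves only from 98.5% to 98.4%, and NPV = 1 − r. Bounds are therefore wide for sensitivity and tight for specificity, and that specificity is nowhere near the naive values in step 3.

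**5. What the design does give.** PPV half-width = 1.96 x √(p(1 − p)/450): 4.2 points at p = 30% or 70%, and 4.6 points at 50%. Yield = 3% x PPV: 9 to 21 confirmed cases per 1,000 screened for PPV 30% to 70%. Both assume that refusing biopsy is unrelated to fibrosis, or is handled by weighting, which would widen the interval somewhat.

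**The case against.** The strongest reply is that the restriction is already declared: the outcome is limited to participants with a visit-2 biopsy. That is true, but the clause does not remove selection on the index test, and the outcome still names the general population. A full SAP might add a correction for attendance and refusal, and its absence from the article is no finding. No SAP, however, can supply histology for a stratum with zero chance of biopsy.

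Other parts of the defence stand and limit the point:

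- A reader might infer that nothing about VCTE accuracy can be estimated. That goes too far. PPV among positives is estimable. The negative row need not be empty, because ALT referral, suspected disease and the repeat LSM at visit 2 can all fill it. The planned 5-year comparison by LSM group also gives outcome evidence on negatives, though not histology.
- A reader might infer that naive sensitivity must come out near 99%. That holds only if negatives are biopsied at random. With disease-enriched negatives it can be 67% to 76% (step 3).
- A reader might extend the empty-row argument to CAP against ultrasound. Referral does not depend on CAP, so that mechanism does not apply. The fibrosis scores do not decide referral either. For these comparisons the issue is a selected, referred sample.
- The plan names no kappa, and does not expressly plan sensitivity and specificity of LSM against biopsy.
- Partial verification is inherent in a screening study where biopsy follows standard of care. This is a reason to narrow the claim, not to biopsy more people.

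**Conclusion.** The point holds for LSM against biopsy. The referral rule and the biopsy count, taken together, cannot deliver general-population accuracy or concordance. Sensitivity, specificity, NPV and agreement are not identified, because participants with valid LSM < 8 kPa and ALT < 1.5 x ULN are never verified. That conclusion needs no assumed figure.

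The sizes do rest on assumptions. At PPV 50%, sensitivity could lie anywhere from 34% to 100% for fibrosis rates of 3% to 0% among LSM-negatives. Naive specificity in the examples is 0% to 52%, against about 98%. The amount of bias in sensitivity cannot be settled from the documents.

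A reader might also infer that a standard verification-bias correction would rescue the accuracy estimates, or that the main result is undermined. Neither is supported. Such corrections fail where the verification probability is zero unless an untestable assumption is added, which leaves only bounds. The primary outcome, the percentage with LSM ≥ 8 kPa, does not use biopsy.

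**What to change.** Amend Secondary outcome measures, Sample size calculation and Statistical analyses as follows.

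1. Restate the VCTE-biopsy outcome as the PPV of LSM ≥ 8 kPa and the number of biopsy-confirmed cases per 1,000 screened, each at one named histological stage with a 95% CI.
2. Weight both for visit-2 attendance and biopsy acceptance using visit-1 data such as LSM, ALT, BMI, diabetes, age and centre.
3. Relabel the biopsy outcomes as *among referred participants*. Do the same for the ultrasound outcome, giving referral selection as the only reason.
4. Replace the concordance rationale for the biopsy count with PPV precision: about ±4.2 to 4.6 points with 450 biopsies, before any loss from weighting.
5. Present any sensitivity or specificity of LSM only as bounds over stated fibrosis rates in the unverified LSM < 8 kPa group, as in step 4 of the working.

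The cost is wording plus a weighted analysis of data already collected. No extra biopsies and no change to clinical care are needed. The downside is a narrower accuracy claim.

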
#### Recruitment and enrollment of participants

This is a European multicentre clinical research study undertaken in the general population without known liver disease. Participating countries are Denmark, United Kingdom, France, Germany, Netherlands, Italy, Croatia and Spain. LiverScreen recruiting sites (primary care centres and university hospitals) are described in Additional File 1.

Subjects aged 40 years and older, without known liver disease, from the general population will be eligible for the study. Eligible patients will be identified following EU general data protection regulation (GDPR-2018) and will be contacted either by: 1/ general practitioners or primary care nurses; 2/ electronic records at primary care centres, or; 3/ zip code registry. In the first scenario, general practitioners and primary care nurses will randomly invite walk-in subjects of their respective primary care centres to participate in the study. In the second and third scenarios, subjects will be randomly invited to participate through phone calls or postal letters. In the third scenario, subjects will be electronically invited to participate based on random drawing of social security numbers. Once subjects accept to participate in the study, they will be given an appointment at the primary care center or research facility where they will be informed about the details of the study and enrolled if they meet the inclusion/exclusion criteria outlined below.

##### Inclusion criteria

Age ≥ 40 years.Able to give informed consent.

##### Exclusion criteria

Patients meeting 1 or more of the following criteria cannot be selected:Previously known chronic liver disease (including cholestasis). Patients with already known liver steatosis but no diagnosis of liver fibrosis or cirrhosis can be included.Subjects with mental incapacity, language barrier, insufficient social support or any other reason considered by the investigator precluding adequate understanding or cooperation in the study.Subjects with a history of current malignancy including solid tumors and hematologic disorders.Subjects with significant extrahepatic disease that may impair short-term prognosis (including congestive heart failure New York Heart Association Grade IV, chronic obstructive pulmonary disease (COPD) GOLD > 3).Subjects with kidney disease (serum creatinine > 3 mg/dL or undergoing renal replacement therapy).

#### Premature withdrawal

A subject is free to withdraw from the study at any time. In addition, the investigator may decide, for reasons of medical prudence, to remove the subject from the study. The date and reasons for stopping the study will be clearly stated on the subject’s case report form and source document.

#### Measurements and investigation procedures

Measurements and investigations will follow the study plan outlined in Table 1.

**Table 1 Tab1:** Study procedures

STUDY PROCEDURES	VISIT 1	VISIT 2
Informed consent	**X**	
Inclusion/exclusion criteria	**X**	
Medical/surgical history	**X**	**X**
Vital signs	**X**	**X**
Physical examination	**X**	**X**
Concomitant medication	**X**	**X**
Alcohol consumption questionnaire (AUDIT)	**X**	**X**
Quality of life questionnaires (EuroQoL 5d-3)	**X**	
Health survey (SF-12)	**X**	
**LABORATORY ASSESSMENTS**		
HCV/HBV serologies	**X**	
ALT/AST levels	**X**	**X**
GGT/AP levels	**X**	**X**
Haematology	**X**	
Biochemistry	**X**	
Coagulation	**X**	
Leucocyte and CRP	**X**	
Antibodies for autoimmune and celiac diseases		**X**
Biochemistry: TSH, ceruloplasmin, α1AT, bilirubin		**X**
**BIOBANK**		
Blood samples: plasma, serum, DNA.	**X**	
**VC TRANSIENT ELASTOGRAPHY**	**X**	**X**
**ABDOMINAL ULTRASOUND**		**X**
**LIVER BIOPSY**		**X**
**AE assessment**	**X**	**X**

*AE* adverse event, *AP* alkaline phosphatase, *α1AT* α1-antitrypsin, *CRP* C-reactive protein, *HBV* hepatitis B virus, *HCV* hepatitis C virus, *TSH* thyroid stimulating hormone

**Liver fibrosis** will be estimated by three different methods: LSM, liver fibrosis scores and liver biopsy.LSM will be performed in all patients using VCTE. LSM will be performed with M or XL probe following the Automatic Probe Selection tool available on the Fibroscan®. LSM will be repeated at visit 2 in those patients referred to the university hospital. Significant liver fibrosis by VCTE will be defined by a LSM ≥ 8.0 kPa with either M or XL probe.Fibrosis scores/serum biomarkers: Four different established liver fibrosis scores using different blood tests will be determined at visit 1: NAFLD fibrosis score (NFS), Forns Index, Fibrosis-4 (FIB-4) and AST to Platelet Ratio Index (APRI). Significant liver fibrosis will be defined when the values of the different scores are above the following cut-offs, according to literature [8, 10]: NFS ≥ 0.676, Forns index ≥ 6.9, FIB-4 ≥ 2.67, APRI ≥ 1.50.Liver biopsy. In patients with a liver biopsy available, liver fibrosis will be assessed and defined according to SAF/NASH CRN Score [21] and analyzed by two central readers. Discrepancies between two readers will be re-assessed and discussed until consensus.

**Liver steatosis** will be estimated using four different methods, CAP, abdominal ultrasound, liver steatosis scores and liver biopsy.Liver steatosis measured by transient elastography. CAP using VCTE with either M or XL probe will be measured at the time of LSM. Liver steatosis will be diagnosed when the value of CAP ≥ 250 dB/m [22].Liver steatosis measured by abdominal ultrasound. Patients referred to visit 2 will be evaluated by the hepatologist, and an abdominal ultrasound will be performed. Liver steatosis assessed by ultrasound will be graded semiquantitatively (mild, moderate and severe) [23].Liver steatosis measured by steatosis scores. Five different liver steatosis scores using different blood tests will be determined, including FLI, HSI, LAP, ION, NAFLD- LFS, and compared to CAP values. Significant liver steatosis will be defined when the values of the different scores are above the following cut-offs, according to literature [24]: FLI ≥ 60, HSI > 36, LAP ≥ 80, ION ≥ 22, NAFLD-LFS ≥ -0.640.Liver steatosis measured by liver biopsy. In patients with a liver biopsy available, liver steatosis will be assessed in histological samples and defined according to SAF/NASH CRN Score [21] and analyzed by two central readers.

#### Sample size calculation

The sample size for the LiverScreen project has been computed to answer the questions of 1/ the usefulness of TE as a screening method to detect significant liver fibrosis among the European general population ≥ 40 years, and 2/ the differences (if any) in the 5-year incidence of liver clinical outcomes (or cardiovascular events or mortality) between those with and without significant liver fibrosis (LSM ≥ 8 kPa). Because the gold standard for the staging of liver fibrosis remains liver biopsy, the sample size calculation of the study considers the final number of liver biopsies needed to evaluate the concordance between liver biopsy and VCTE. For an estimated prevalence of LSM ≥ 8 kPa of around 3%, assuming a 5% of bilateral alpha error and a statistical power of 95%, a sample size of 28,887 subjects would be required. If 3% of the study population have altered VCTE and only 50% of them agree to have a liver biopsy performed, we will have around 450-500 available liver biopsies. Considering all these factors, the sample size of the study will be of 30,000 subjects.

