### Statistical analyses

Categorical parameters will be presented by means of frequencies (%). Continuous parameters will be summarized by mean ± standard deviation or median and interquartile range, where appropriate. All patients having a VCTE examination with valid measurements [8] will be included in the analysis population. Subjects excluded from the analysis will be compared to those having a VCTE examination with valid measurements using the Chi squared test and t-test for categorical or continuous characteristics respectively. Prevalence and its 95% confidence intervals (95%CI) of LSM ≥ 8 kPa will be computed overall (primary endpoint) and in the subgroup of patients with risk factors. Analogously, prevalence of CAP ≥ 250 dB/m and its 95%CI will be computed, overall and among patients with risk factors. Concordance between variables (LSM, fibrosis scores, CAP, steatosis scores, liver biopsy) will be computed. Scatter plots and Pearson’ r linear correlation coefficients will be used to explore the relationship between continuous variables, including LSM and fibrosis scores values. Receiver operating characteristic (ROC) curves, using LSM ≥ 8 kPa as the gold standard for fibrosis, will be computed for the different continuous fibrosis scores. Sensitivity, specificity, predictive values and likelihood ratios will be performed using LSM ≥ 8 kPa as the gold standard for fibrosis for different fibrosis categorized scores. Comparison of values obtained with M and XL probes in the assessment of LSM and CAP will be performed both, using the continuous forms of the variables with t tests (or non-parametric tests in the case these variables violate the necessary assumptions), and using the categorical variables using the 8 kPa and 250 dB/m^2^ cut-offs with Chi squared test. In addition, multivariate linear regression models and multivariate logistic regression models will be computed with LSM (or CAP) as the dependent variable (continuous for linear model and categorical for logistic mode) to assess the effect of the M or XL and potential interaction with the probe size. The relative frequency of adverse events to the study procedures will be reported in percent.

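### The 28,887 subjects are justified by a 95% power that belongs to no stated comparison, the 5-year objective has no stated assumptions, and the biopsy inputs give 450, not up to 500

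*Protocol article*

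**What the plan says.** All of the sizing is in the section Sample size calculation of the protocol article. It names two questions that the size was computed to answer. One is the usefulness of transient elastography for screening. The other is "the differences (if any) in the 5-year incidence of liver clinical outcomes" (or of cardiovascular events or mortality) between people with and without LSM ≥ 8 kPa. It adds that the number of biopsies needed for concordance with elastography was considered, but does not state that number.

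The only numerical inputs to the main figure are a prevalence of around 3%, a two-sided alpha of 5% and a power of 95%. After the prevalence, the text reads: "assuming a 5% of bilateral alpha error and a statistical power of 95%, a sample size of 28,887 subjects would be required". For biopsies, the section takes 3% with altered elastography and says that if "only 50% of them agree to have a liver biopsy performed, we will have around 450-500 available liver biopsies". The final size is set at 30,000.

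The primary outcome is a percentage of subjects. Under Statistical analyses, the prevalence of LSM ≥ 8 kPa and its 95% confidence interval "will be computed overall (primary endpoint) and in the subgroup of patients with risk factors". No reference value and no test are given for it.

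**The concern.** Power is the probability of rejecting a null hypothesis when a specified alternative is true. Without an alternative, a prevalence, an alpha and a power do not determine a sample size. A prevalence reported with a confidence interval has a precision, not a power. As written, a reader would take the study to have 95% power for its primary question, when no analysis described for that question has a power at all.

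The second sizing question is a real comparison to which power could apply. Whether 28,887 is enough for it depends on the background 5-year incidence and the effect to be detected, and neither is printed.

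The biopsy count matters because it fixes how well elastography can be judged against histology. A range that starts at the value the inputs give and runs only upwards is more favourable than those inputs.

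**Working it through.** **Inputs from the article:** prevalence p = 0.03; two-sided alpha 0.05 (z = 1.960); power 95% (z = 1.645); stated N = 28,887; final N = 30,000; biopsy acceptance 50%. **Assumed here, because the article gives no values:** the 5-year background incidence (0.5%, 1%, 2%), full follow-up and simple random sampling.

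**1. Can 28,887 be reproduced?**

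*As precision,* n = 1.96² × p(1 − p) / d². Power plays no part.
- p = 3%, d = 0.20 points: 3.8416 × 0.0291 / 0.000004 ≈ 27,947, which is 3.3% below 28,887.
- p = 3%, d = 0.15 points: 49,683; d = 0.25 points: 17,886.
- p = 3.1%, d = 0.20 points: about 28,848, within 0.2% of 28,887.

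*As a one-sample two-sided test at 95% power,* n = [1.960√(p0(1 − p0)) + 1.645√(p1(1 − p1))]² / (p1 − p0)².
- 3.0% against 3.5%: 16,213; against 3.3%: 43,845; against 2.5%: 13,979.
- Solving for n = 28,887 gives an alternative of about 3.37% or 2.65%, a shift of 0.35 to 0.37 points. The article mentions no such shift.

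Several unstated assumptions come close to 28,887, and the printed inputs select none of them.

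*Precision actually delivered,* half-width = 1.96 × √(0.03 × 0.97 / N): 0.197 points at 28,887 and 0.193 points at 30,000.

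**2. The 5-year comparison.** A 3% prevalence splits 28,887 into about 867 and 28,020. The two-proportion formula with pooled variance under the null and allocation ratio k = 97/3 is

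n1 = [1.960√((1 + 1/k) p̄(1 − p̄)) + 1.645√(p1(1 − p1) + p0(1 − p0)/k)]² / (p1 − p0)², with total n1(1 + k) and p̄ = (p1 + k·p0)/(1 + k).

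| Assumed background incidence | Relative risk detectable at 95% power, N = 28,887 | Total needed for relative risk 2 |
|---|---|---|
| 0.5% | about 3.4 (0.5% v 1.72%) | about 126,000 |
| 1% | about 2.6 (1% v 2.58%) | about 62,500 |
| 2% | about 2.0 | about 30,767 |

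For a relative risk of 2, the same N is nearly enough at 2% and more than fourfold too small at 0.5% (126,000 / 28,887 = 4.4). Loss to follow-up would raise these requirements.

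**3. Biopsies,** N × 0.03 × 0.50.
- 30,000 × 0.03 × 0.50 = 450, the low end of the stated range.
- 28,887 × 0.03 × 0.50 = 433, below the range.
- For 500 at N = 30,000: prevalence 500 / (0.5 × 30,000) = 3.33%, or acceptance 500 / 900 = 55.6%.

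Precision for a proportion of 50% at n = 450: 1.96 × √(0.25 / 450) = ±4.6 points.

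**The case against.** The strongest reply is that nothing here shows an error in 28,887. The prevalence is only approximate, and 3.1% with a half-width of 0.2 points gives 28,848. A test of 2.65% against 3% needs about 28,938. This stands: a reader might infer that the figure is numerically wrong, and the article does not support that. It supports only that the figure cannot be derived from what is printed.

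The reply also notes that the power sentence may belong to the 5-year comparison. Alpha, power and a 3% exposed fraction would all enter such a calculation, many pairs of incidences give a total within 3% of 28,887, and the assumptions may be in the full protocol, which is not shown. This stands too. It would be tempting to say that the longitudinal comparison was never sized, but that is unproven. The article still attaches its power to a prevalence and leaves unnamed the comparison it belongs to.

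On biopsies, both the prevalence and the yield are approximate, and 450 is reproduced at the final N. It is tempting to call 450 a ceiling, or to cut it further for missed second visits and lower repeat readings. The article supports neither step. Under Study design, biopsy may also be offered when chronic liver disease is suspected, and raised ALT or failed elastography also leads to visit 2. Repeat measurement with both probes can add positives as well as remove them. Non-attenders are referred again, and the 50% may already allow for those who do not come. Any reduced count would rest on rates found nowhere in the document. What remains is that the paragraph's own multiplication gives 450 and does not reach 500.

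**Conclusion.** The point holds, with moderate importance. The article states a 95% power that does not apply to its primary analysis, and a required size that its printed inputs do not determine. It names the 5-year comparison as a basis for the size without the incidence or effect assumed. With 28,887 subjects, a 3:97 split and no losses, 95% power is reached only for a relative risk of about 3.4, 2.6 or 2.0 at background incidences of 0.5%, 1% or 2%. Those incidences are assumptions made here, not values from the trial. The biopsy inputs give 450 at 30,000 (433 at 28,887). The upper end of 500 is 11% above 450.

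The choice of 30,000 is not in question for the primary estimate. A half-width of about 0.19 points at 3% is ample, and nothing found here would bias that estimate or invalidate its interval. The fault is in the stated justification.

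**What to change.** In the section Sample size calculation:

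- State the primary justification as precision: 30,000 subjects give a 95% confidence interval of about ±0.19 percentage points at a prevalence of 3%, under simple random sampling. Remove the 95% power, or attach it to a named comparison with the difference to be detected.
- State the 5-year difference detectable with about 900 v 29,100 subjects, with the assumed background incidence and loss to follow-up. Otherwise, drop that objective as a basis for the size.
- Replace the range of 450-500 with about 450 biopsies from altered elastography, if the 50% already includes non-attendance at visit 2. Add the precision this gives, about ±4.6 points for a proportion of 50%.

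If the full protocol holds the assumptions behind 28,887, quoting them would settle the first two items. The cost is text only, with no extra participants and no change to procedures. The stated figures become slightly less favourable.
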